## Abstract

**Background:**

Older adults with cancer struggle to maintain recommended levels of physical activity and nutrition during treatments. Collecting data in a real-life context provides a better understanding of the motivational and behavioral dynamics of this population, which is underrepresented in clinical trials. Ecological momentary assessment (EMA) is a frequently used approach to collect repeated measures in real time in a naturalistic environment. This approach can provide insights into the temporal dynamics of psychological processes, such as motivation toward health behaviors. The aim of this study is to identify clusters based on predictive motivational variables related to physical activity and nutritional behaviors among older patients with cancer, via repeated measures.

**Methods:**

In this project, older patients with a cancer (≥ 70 years old) complete physical capacity assessments, malnutrition identification, and a comprehensive geriatric assessment with G-code. After that, participants engage in a 2-week data collection protocol combining EMA and sensor-based monitoring of behavior. The participants wear an ActiGraph GT3X-BT accelerometer (ActiGraph, LLC) on their nondominant waist to measure physical activity. EMA questionnaires are delivered 3 times per day - morning (between 8am and 10am), midday (between 12pm and 2pm) and evening (between 7pm and 8pm) - via smartphones or computers with the UniQ digital application. Motivational constructs based on the Theory of Planned Behavior are collected in the morning and at midday. Nutritional behavior data are collected at midday and in the evening. Fatigue is collected in the morning, at midday and in the evening. The data analysis strategy shall include Multilevel Vector Autoregressive Models with k-means clustering.

**Discussion:**

This project seeks to identify clusters in older patients with cancer based on key motivational predictors related to physical activity and nutritional behaviors, via approaches for collecting repeated measurements in real time within a naturalistic environment. This research into the mechanisms of action between motivation and behaviors could optimize care pathways by designing appropriate intervention content, under conditions where the content will be most effective, to promote sustained behavior change among older adults with cancer.

**Trial registration:**

ClinicalTrials.gov (NCT06445140). Registered on 06 June 2024.

**Supplementary Information:**

The online version contains supplementary material available at 10.1186/s12877-025-06130-1.

## Introduction

While cancer is the leading cause of death in people aged 75 to 85, and the second leading cause of death in people over 85, there is little evidence concerning the elderly due to their under-representation in clinical trials [1]. This underrepresentation increases the risk of under or overtreatment in this population [2], making the elderly even more vulnerable to chemotherapy-related toxicities [3]. There is considerable heterogeneity in the population of patients over 70 years old. Some individuals age with few comorbidities and maintain independence, whereas others have several chronic pathologies and deficits [4]. Support for the elderly cancer patients must be comprehensive and individualized, incorporating their opinion and a multidisciplinary approach to meet all identified needs [5].

Aging leads to physiological changes (hormonal, metabolic, etc.) and an increase in risk behaviors, including physical inactivity and malnutrition [6–8]. These factors are responsible for a loss of strength and muscle mass [9], exacerbated by cancer and its treatments [10], a phenomenon that is even more pronounced in elderly individuals. This progressive and generalized loss of muscle mass and strength is associated with a deterioration in physical capacity and high rates of hospitalization and mortality [10]. In addition to muscle-related issues, these risky behaviors associated with aging also lead to the onset of other comorbidities and a higher risk of mortality [11].

In this context, nutritional support and physical activity (PA) programs / prescription are two complementary and effective interventions for maintaining muscle status and preventing malnutrition during oncology treatment. More specifically, prevention and management of this loss of muscle mass and strength should be based on adequate energy and protein intake [9, 12] and multimodal exercise (including muscle strengthening coupled with exercise conditioning) at moderate intensity [8, 9, 12–14]. These recommendations apply to both primary, age-related mass loss, and secondary, disease-related mass loss. Although an intervention combining nutritional support and regular PA practices is recognized as effective, it is difficult to achieve high adherence [13, 15], and lasting behavioral changes interventions are needed to encourage the elderly to adopt a more active lifestyle [16] and to change their eating habits [17].

Identifying the motivational variables associated with PA and nutrition in this population could facilitate the adoption and sustainability of these behaviors. Past literature indicates that using a theoretical approach to identify motivational variables associated with PA and nutrition is important to facilitate behavior change and increased adherence [18, 19]. A meta-analysis has shown that no theory is superior to another in terms of effectiveness in changing PA, and that interventions are more effective when they are based on a single theory rather than a combination of theories [18]. In this respect, the theory of planned behavior (TPB) is commonly used in behavior change studies, particularly for an aging population [19, 20]. This theory assumes that the adoption of a behavior arises from the formation of intentions in the individual, which is the most important determinant of behavior [20, 21]. These intentions are facilitated by attitudes, subjective norms (particularly perceived in the caregiver) and perceived behavioral control. Attitudes represent the benefits perceived by the characteristics of the perceived outcome expectancy, forming two distinct types of attitudes: affective attitudes, the emotion and affect-based perceptions about a behavior (e.g., dull or pleasant); and, instrumental attitudes, the perceptions related to the usefulness (e.g., worthless or valuable). Subjective norms correspond to the individual’s social influence, represented by what those around him or her think of the behavior he or she wants to undertake. Perceived behavioral control refers to the perceived ease or difficulty of performing a behavior, and thus to an individual’s belief that he or she possesses the necessary resources to perform the behavior. Moreover, this variable is assumed to be directly related to behavior. In oncology and geriatrics, intervention research indicates that an increase in TPB variables is accompanied by a significant increase in PA levels [20, 22].

However, the TPB has been criticized for its fluctuating prediction of behavioral intentions. Indeed, the designs used are often based on a limited number of measures, failing to consider the temporal fluctuation of perceptions and intraindividual variability [18]. In response to these methodological limitations, repeated-measures methods are relevant to assess the relationship between intentions and behavior on a daily basis [23, 24]. In particular, intentions can vary according to the time of day, reflecting the dynamics of motivational variables [24]. As a result, repeated-measures methods are deemed effective to estimate TPB variables and the intention-behavior gap, as they identify the contexts most conducive to a translation of intentions into action [23].

Ecological Momentary Assessment (EMA) involves repeated sampling of behaviors and experiences, which could consider the temporal fluctuation of perceptions in the subject’s natural environment [25, 26]. The EMA aims to minimize recall bias, maximize ecological validity, and allows the study of microprocesses that influence behavior in real-world contexts. This data collection method is suitable for measuring TPB variables and could improve their predictive ability. Older adults constitute a population particularly amenable to EMA research [27], with high compliance rates (around 80%) [25, 28]. Collecting repeated measures in real time within a naturalistic environment, like wearables technologies and EMA [27], is crucial for a better understanding of the behaviors for this specific population [29]. By improving the observability and feasibility of the components of an intervention, it becomes possible to develop effective, individualized interventions that consider the singularity of individuals and their situation. With the aim of developing an optimal behavior-change intervention for elderly cancer patients, further research is needed to understand the mechanisms of action on PA and nutritional behaviors.

## Materials and methods

### Study design

This is the protocol of the observational part of MONAGE, a prospective longitudinal observational cohort study, taking place over a period of 2 weeks, with a longitudinal ecological momentary assessment (EMA) phase and GT3X accelerometer worn on the waist.

The aims of the observational part of MONAGE are to identify motivational predictors related to PA and to nutritional behaviors and to observe groups of patients with similar patterns of relations between motivation and behaviors among older patients with cancer.

### Patient selection

Recruitment is anticipated to be completed by April 2026, with the aim of enrolling 40 patients in total. The patients considered for inclusion are those who come for their oncogeriatric care at the Cancer Institute of Montpellier (ICM) which is referral centre in France. If patients are eligible, the study is proposed to them by the investigator. Patients have to meet the following inclusion criteria: being aged 70 or over, having cancer (solid tumors, all sites), having a Geriatric 8 (G8) score ≤ 14, being inactive, i.e., not meeting recommended PA levels of 150 min per week at moderate intensity, providing informed, written and expressed consent and having a social security affiliation.

The exclusion criteria are as follows: known presence of brain metastases, inability to participate in digital platform or physical tests, inability to eat orally, contraindication or inability to engage in PA, inability to follow up regularly for psychological, family, numerical, social or geographical reasons and lack of liberty or under protective custody or guardianship.

This research will be conducted in accordance with the French Public Health Code, the Good Clinical Practice and the Declaration of Helsinki. This study has been registered on clinicaltrial.gov (NCT06445140). This research project has been approved by the national ethics committee (Comité des Personnes Nord Ouest III, accepted on 30 May 2024) and the “Agence nationale de sécurité du médicament et des produits de santé” (ANSM, French National Agency Authority for the Safety of Health Products) has been informed (19 June 2024). Written informed consent was obtained from all participants prior to inclusion in the study. Data will be securely stored using EasyMedStat software.

### Procedures

#### Baseline assessments and consultations

As part of usual care, the patient takes part in three consultations: one with a geriatric oncologist, one with a teacher in adapted physical activity (kinesiologist) and one with a dietician. Figure 1 provides an overview of the study design and assessments.

**Fig. 1 Fig1:**
[figure not shown]
Overview of the study’s design and procedures

#### Oncogeriatric consultation

The patient takes part in a Comprehensive Geriatric Assessment (CGA), with a geriatric oncologist, to facilitate appropriate geriatric management. CGA is a patient-centered, multidimensional, and interdisciplinary process that results in a personalized care plan, identifying and addressing health issues that may contribute to frailty [30]. The International Society of Geriatric Oncology (SIOG) and the American Society of Clinical Oncology (ASCO) recommend incorporating geriatric assessments in the care of older patients with cancer [31]. During this consultation, the CGA includes the Geriatric Core Data Set (G-CODE) [5]. The tools/items proposed for the G-CODE are the following: (1) social assessment: living alone or support requested to stay at home; (2) functional autonomy: Activities of Daily Living (ADL; [32]) questionnaire and short Instrumental ADL questionnaire [33]; (3) mobility: Timed Up and Go test [34]; (4) nutrition: weight loss during the past 6 months and body mass index; (5) cognition: Mini-Cog test [35]; (6) mood: Mini-Geriatric Depression Scale [36] and (7) comorbidity: updated Charlson Comorbidity Index [37].

#### Exercise consultation

The patient takes part in an exercise consultation, with a teacher in adapted physical activity (kinesiologist), to evaluate PA level and capacity. The assessments proposed during the exercise consultation are the following: PA level (Global Physical Activity Questionnaire; [38]), grip strength (Handgrip with Jamar PLUS + Digital Dynamometer; [39]) and lower extremity function (Short Physical Performance Battery; [40]).

Grip strength is a clinically objective test, easy and reproducible, which measures maximum grip strength in the dominant hand by using a hand dynamometer to estimate muscle strength in the upper extremity [41]. The Short Physical Performance Battery is also an objective test designed to assess lower extremity function with three parts (Balance, Gait Speed and Chair Stands). These two objective tests are gaining increasing popularity in oncology, particularly in geriatric settings [42].

During this exercise consultation, the patient is given the Institut National du Cancer (INCa) recommendations for PA [43], which include: at least 150 min of cardiorespiratory exercise at moderate-intensity per week, at least 2 sessions per week of muscle-strengthening exercise, flexibility and mobility exercise 2 to 3 sessions per week and balance exercises at least twice a week for patients aged 65 and older. Patients are clearly informed that the concepts of individualization and progressiveness are fundamental to these recommendations. During this consultation, patients are free to ask any questions they may have. No exercise program is carried out during this consultation. However, if necessary, a prescription for the physiotherapist is given to the patient.

#### Nutritional consultation

The patient takes part in a nutritional consultation, with a dietician, to assess the nutritional status and identify needs for nutritional support, if necessary. The assessments proposed during the nutritional consultation were as follows: dietary intake (Visual/Verbal Analogue Scale of food ingesta (ingesta-VVAS); [44]) and identity nutritional risk (Mini Nutritional Assessments; [45]).

The ingesta-VVAS uses 10-point analogue scales to estimate dietary intake in patients with cancer; higher scores indicate better dietary intake and a score ≤ 7 is used as cut-off value to detect patients with nutritional risk of weight loss in medical oncology [44]. The Mini Nutritional Assessments is a validated tool to identify individuals aged 65 years or older who are at risk of malnutrition or malnourishment [46], with threshold values of ≥ 24 for well-nourished individuals, 17-23.5 for those at risk of malnutrition, and < 17 for malnourished individuals, with good validity scores [47].

During this nutritional consultation, on the basis of the European Society for Clinical Nutrition and Metabolism (ESPEN) recommendations for nutrition in geriatrics [48] and in cancer [49], the patient is given the following 3 recommendations: incorporate foods rich in protein and calories in the diet; eat small portions multiple times a day to ensure adequate intake; and drink water between meals to maintain appetite. During this consultation, patients are free to ask any questions they may have. If necessary, a prescription for oral nutritional supplements is given to the patient.

#### Preparation for data collection

At the end of the 3 consultations, if the selection criteria are validated by the geriatric oncologist and by the kinesiologist for the level of PA, the study is fully explained by the investigator. Examples of data collection questions and applications are shown to the patient on the phone and/or computer.

If the patient accepts and signs the consent form directly, a personal account is created on the digital platform “UniQ”. If the patient decides to use it on his / her phone, the investigator installs the application, adds it to the home screen, and makes the first connection with the patient. If Uniq is used on a computer, an account is created, and an email is sent to the patient to activate the account from his / her computer. A phone number is also provided to patients for support in case of technical issues.

### Outcomes measures

Data collection begins the day after inclusion and lasts for 14 days. The data are collected via digital scales on the UniQ application via an EMA approach and a GT3X accelerometer worn on the waist. To observe whether the protocol seemed feasible for patients during the creation of the intervention, 7 patients with similar profile to those likely to be included were questioned about the frequency and duration of data collection. The retained configuration (i.e., answering to 3 very short questionnaires per day, and wearing the accelerometer for 14 days) suited both the patients and the investigators. The estimated time taken to complete the 3 questionnaires for a patient is 10 min per day, i.e. 4 min for the morning and midday questionnaires (12 items) and 2 min for the evening questionnaire (2 items). Every time a questionnaire is sent, patients receive an automatic e-mail informing them that a questionnaire is available on their UniQ platform and inviting them to answer. If necessary, the patient is informed that the caregiver can help him to complete the questionnaires.

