### Statistical analysis

The objective of our study is to identify clusters based on predictive motivational variables related to PA and nutritional behaviors among older patients with cancer. The analyses to be conducted aim (i) to identify predictors of PA and nutritional behaviors and (ii) to identify groups of patients with similar patterns of relations between motivation and behavior.

We will evaluate the sample’s adherence to and acceptance of this original data collection with descriptive statistics such as the means, medians, and percentages. These measures will allow us to summarize the key characteristics of the dataset.

For the first step, we will use a Multilevel Vector-autoregressive model (mlVAR), as implemented in the R package “mlVAR.”. mlVAR model will be run in parallel for physical activity and nutrition separately. The mlVAR is a multilevel extension of the vector auto-regression (VAR) model, which describes dynamic relationships among variables measured repeatedly over time from multiple subjects [58]. This model has become a popular tool particularly in studies involving psychological variables [59]. In a contemporaneous network, mlVAR identifies relationships between variables over the same time interval. To observe the temporal dynamics between variables in mlVAR, lagged coefficients quantify the auto-regressive effect (one variable on itself) and cross-lagged effect (one variable on another variable). In this temporal network, these coefficients illustrate the predictive relationships between variables over time and identify potential causal relationships. As a hypothetical example, we can observe that intention at time *t* predicts behavior at time *t + 1*, suggesting a directional influence of intention on subsequent behavior over time.

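### If motivation and behavior drift together over the 14 days after counselling, the stated mlVAR can report the shared trend as motivation predicting behavior

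*Protocol article*

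**What the plan says.** **Timing.** Under Preparation for data collection, the study is offered after counselling: "At the end of the 3 consultations, if the selection criteria are validated by the geriatric oncologist and by the kinesiologist". Enrolment on the spot is possible but conditional: "If the patient accepts and signs the consent form directly, a personal account is created on the digital platform". Outcomes measures then fixes the start: "Data collection begins the day after inclusion and lasts for 14 days". No lead-in or discarded first days are described.

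**What comes before the window.** Exercise consultation: "During this exercise consultation, the patient is given the Institut National du Cancer (INCa) recommendations for PA", with a physiotherapy prescription where needed. Nutritional consultation: "the patient is given the following 3 recommendations: incorporate foods rich in protein and calories in the diet", and two further pieces of advice, with oral supplements prescribed where needed. The Procedures section presents all three consultations as usual care.

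**Analysis.** Statistical analysis names mlVAR, run separately for activity and nutrition, and says of the lagged terms that "these coefficients illustrate the predictive relationships between variables over time and identify potential causal relationships". K-means then uses the VAR coefficients. Creation of an intervention matches later patients to the clusters and offers a technique only where the relevant construct was a significant predictor. The only preprocessing step that deals with patterns over time is Kalman imputation, which fills gaps and does not remove a trend. Strengths and limitations mentions neither counselling carry-over nor drift.

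**The concern.** A lag-1 vector autoregression treats each person's series as varying around one stable mean. This design gives a specific reason to doubt that. Inactive patients are advised on the two behaviors about to be measured. They also begin three daily prompts and a waist device together. Motivation and behavior could both start high and fade, or both rise as advice takes hold.

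Either way, an early high motivation score is followed by a high behavior score simply because both are early. The model without a trend term credits this to the lagged motivation coefficient. This is a trend across days, distinct from any morning-afternoon difference.

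Both aims rest on these coefficients, and intervention content is to be chosen from whichever construct turns out significant.

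**Working it through.** The article gives no effect size, alpha or derivation for this analysis, so there is no figure to reproduce. The check asks how large a shared drift must be before it matters.

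**Inputs from the article.** 40 patients (Patient selection); 14 days (Outcomes measures); motivation twice daily and two activity segments per day. That is 14 × 2 = 28 occasions and 27 lag-1 pairs per patient.

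**Assumptions, not in the article.** Within-person SD 1; autocorrelation 0.3 in every series; true motivation-to-behavior cross-lag 0; a drift of d SD over the window shared by all series, either linear or exponential with a 4-day time constant. The fit is a person-mean-centered lag-1 regression with person-clustered standard errors, which approximates the within-person temporal part of mlVAR.

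**Step 1: expected false coefficient, one predictor.** A linear drift over 28 points adds variance v = d² × (28² − 1)/(12 × 27²) = 0.0895 d² to each series, and about the same amount to every covariance between them. The normal equations have matrix [1+v, v; v, 1+v] and right-hand side [v; 0.3+v], so

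β = [v(1+v) − v(0.3+v)] / [(1+v)² − v²] = 0.7v/(1+2v).

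- d = 0.5: v = 0.0224, β = 0.0157/1.045 = 0.015
- d = 1.0: v = 0.0895, β = 0.0627/1.179 = 0.053
- d = 1.5: v = 0.2014, β = 0.1410/1.403 = 0.100

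**Step 2: simulation, one predictor, 1000 runs per setting.** Share of runs with a significant positive coefficient (nominal 2.5%):

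| Drift (SD) | Mean false β, linear | Linear | Exponential | Linear drift, detrended | Exponential drift, linearly detrended |
|---|---|---|---|---|---|
| 0 | 0.000 | 3.1% | 3.4% | 3.1% | 2.8% |
| 0.25 | 0.004 | 3.7% | 3.7% | 3.1% | 2.6% |
| 0.5 | 0.016 | 8.2% | 6.8% | 2.7% | 4.2% |
| 0.75 | 0.035 | 23.1% | 13.3% | 3.0% | 4.3% |
| 1.0 | 0.054 | 46.5% | 31.0% | 2.5% | 3.9% |
| 1.5 | 0.105 | 95.5% | 85.2% | 2.4% | 10.2% |

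The simulated coefficients agree with Step 1. A separate simulation gave about 5%, 55% and 96% for linear drifts of 0.5, 1 and 1.5 SD. Using within-day lags only, the rates at 1 SD are 32.2% (linear) and 24.2% (exponential).

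**Step 3: six predictors** (five Theory of Planned Behavior items plus fatigue, correlated 0.4, all sharing the drift), linear drift of 1 SD.

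- Per coefficient: 6.7% and 7.9% in two sets of runs; a smaller 300-run check gave 11%.
- At least one false predictor: 37% of runs, against 16% with no drift.
- Sum of the predictor coefficients: about 0.10, falsely significant in 71% of runs.
- After detrending: 15% for any false predictor and 3% for the sum.

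**Step 4: how firm is the 70%?** I repeated Step 3 with 2000 runs. The sum of all six was falsely significant in 75% of runs when behavior had no same-occasion correlation with the predictors, and in 50% when that correlation was 0.4. Summing only the five motivation items gave 43% and 32%. The same correlation also lowers the one-predictor rate at 1 SD, to 25%. Detrending brought all of these back to about 3%.

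**The case against.** **Silence in a condensed article.** Trend checks often sit in a full protocol or analysis plan that is not shown, so the absence of detrending is not a finding by itself. That stands. What the article does state is the start rule, the causal reading and the use of the coefficients, and that combination is unsafe under a shared trend.

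**The drift is assumed.** No passage describes a fading effect or its size. No exercise program is carried out at the consultation, and prescriptions are given only where needed. A reader might infer that a counselling effect will show up as false prediction. The documents do not support that: at 0.25 SD the distortion is negligible and at 0.5 SD it is small.

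**The post-counselling state may be intended.** The consultations are usual care, and the next-day start applies only to patients who sign directly. This answers a complaint about generalizability or about the label observational. It does not answer the unmodelled trend.

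**One predictor is not the planned model.** Correct: with six predictors the rate per coefficient falls to about 7% at 1 SD. The false effect is spread across items, though, not removed.

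**Clusters.** A reader might also infer that patients will be grouped by how fast counselling fades. The one check made does not support this. With drift varying between patients (mean 1 SD, between-patient SD 1), a patient's drift correlated only 0.07 with that patient's own coefficient under six predictors, and 0.29 under one. The coefficient spread was 0.28 without drift and 0.29 with it, so sampling noise dominates. That check used person-level least squares without mlVAR shrinkage.

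**Conclusion.** The concern holds as a conditional one. Collection can start the day after counselling, and the described model has nothing to absorb a trend shared by motivation and behavior. A shared drift of about 0.75 to 1 SD or more would materially inflate the motivation-to-behavior cross-lags; a drift of 0.25 SD would not.

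In a one-predictor model the false-positive rate is about 5-8% at 0.5 SD, 45-55% at 1 SD and 95% at 1.5 SD. With six predictors it is about 7% per coefficient at 1 SD. The summed effect is falsely significant in about 70% of runs in the setting first tested, and in roughly a third to a half if behavior also correlates with the predictors at the same occasion.

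These figures rest on an assumed drift size and shape, autocorrelation 0.3, inter-item correlation 0.4, fatigue drifting in the same direction as motivation, and a regression approximation to mlVAR. They show what could happen, not what will. The change is worth making because it is cheap and, with no drift, left the false-positive rate near nominal.

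**What to change.** 1. Before mlVAR, remove each patient's trend over study day from every motivation, fatigue, nutrition and activity series, or enter study day as a within-person covariate. Cluster on the resulting coefficients.
2. Report the undetrended fit alongside, so that a reader can see how much of each cross-lag depends on the trend.
3. Add a sensitivity analysis that drops days 1-3. A straight line does not fully remove a curved fade: 10.2% false positives remain at an exponential drift of 1.5 SD.
4. In Statistical analysis, replace the phrase on potential causal relationships with: predictive associations between motivation and behavior in the two weeks after usual-care counselling.

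**Cost.** Analysis and wording only, with no new data or visits. Real slow co-variation of motivation and behavior is removed from the main fit, which is why the undetrended fit should be shown too. One degree of freedom per series is used. The sensitivity analysis has 28 − 3 × 2 = 22 half-day occasions per patient, in a study that already lists series length as a limitation.
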